## Abstract

Despite advances in the treatment of Alzheimer’s disease (AD), there is currently no prospect of a cure, and evidence shows that multifactorial interventions can benefit patients. A promising therapeutic alternative is the use of transcranial direct current stimulation (tDCS) simultaneously with cognitive intervention. The combination of these non-pharmacological techniques is apparently a safe and accessible approach. This study protocol aims to compare the efficacy of tDCS and cognitive intervention in a double-blind, randomized and factorial clinical trial. One hundred participants diagnosed with mild-stage AD will be randomized to receive both tDCS and cognitive intervention, tDCS, cognitive intervention, or placebo. The treatment will last 8 weeks, with a 12-month follow-up. The primary outcome will be the improvement of global cognitive functions, evaluated by the AD Assessment Scale, cognitive subscale (ADAS-Cog). The secondary outcomes will include measures of functional, affective, and behavioral components, as well as a neurophysiological marker (Brain-derived neurotrophic factor, BDNF). This study will enable us to assess, both in the short and long term, whether tDCS is more effective than the placebo and to examine the effects of combined therapy (tDCS and cognitive intervention) and isolated treatments (tDCS vs. cognitive intervention) on patients with AD.

**Clinical Trial Registration**: www.ClinicalTrials.gov, identifier NCT02772185—May 5, 2016.

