## Materials and Equipment

### Overview

NeuroAD is a factorial, placebo-controlled, double-blind and randomized clinical trial in which 100 patients at the mild stage of AD are randomly assigned to four groups: 1—active tDCS and active cognitive intervention; 2—sham tDCS and active cognitive intervention; 3—active tDCS and placebo cognitive intervention; and 4—sham tDCS and placebo cognitive intervention. All of the patients will be subjected to tDCS and cognitive intervention applied for 24 workdays. At the end of the trial, patients who received active tDCS and achieved clinical response will be invited to maintain tDCS bimonthly for 12 months, as part of a long-term study of tDCS for AD; those who did receive sham tDCS and did not respond will be offered 24 open-label daily sessions of tDCS (crossover study); finally, those who showed response with cognitive intervention (real or placebo) and sham tDCS will be referred to other neuropsychological centers specialized in treating dementias in our Institution.

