#### Proposed Analysis

Intent-to-treat analysis will be used; that is, all participants will be included in the analysis, including those who drop out before completing the treatment. However, high or different rates of dropouts between the treatment arms may lead to biases. Thus, a sensitivity analysis will be performed with different assignment procedures to assess the value of the data. The best strategy resulting from the following methods will be chosen: last observation carried forward, complete case analysis, likelihood-based methods, or multiple imputation.

Descriptive statistics will be used to describe clinical and sociodemographic characteristics and the primarily and secondary outcomes of each group at the baseline. The groups will be compared by analysis of variance (ANOVA), for continuous variables, or the chi-square test, for categorical variables.

The primary outcome will be examined by split-plot ANOVA with one dependent variable (ADAS-Cog score) and two independent variables, namely, one intra-group variable and one inter-group variable. The within-subject variable will include time (baseline, post-treatment and 12-month follow-up), and the effects of the treatment condition (active or placebo tDCS; active or placebo cognitive intervention) will be examined as a between-groups variable. *Post hoc* comparisons using Bonferroni correction will be performed where appropriate. Finally, the effect sizes regarding inter-group comparisons will be calculated using the eta squared (*η*^2^), and effect sizes regarding intra-group comparisons will be calculated by means of Cohen’s d using Hedges’ correction (Fritz et al., 2012), adopting the significance level of *p* < 0.05. For all variables of the secondary outcomes, the same analysis strategy will be used. Non-parametric tests will be performed if some of the outcomes do not meet the conditions necessary for parametric analysis.

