**Figure 2 F2:**
[figure not shown]
Flowchart of phases I (double-blind factorial clinical trial), II (crossover) and III (follow-up) of the Neurostimulation combined with Cognitive Intervention in Alzheimer’s disease (AD) Study (NeuroAD). T0: Baseline, pre-intervention measurement. T1–T8: intervention, tDCS and cognitive treatment. T9: endpoint, post-intervention measurement.

The phase I is a double-blind, randomized, factorial clinical trial in which tDCS will be applied in parallel to cognitive intervention in AD patients. This stage includes two measurement time points: baseline (week 0) and post-treatment (week 8). The data collection sessions will be performed by treatment-blinded investigators including the primary and secondary outcomes assessments. The pre-measurement consists of a screening and measurement part. The screening part contains data of the DSM-IV-TR, NINCDS-ADRDA criteria, CDR, MMSE and health questionnaire (including questions about disease duration, comorbidities and use of medication). Adverse effects will be assessed at each session, wherein the tDCS rater will ask the patients whether they feel any discomfort or pain and whether this could be related to tDCS.

Phase II is an open-label, crossover phase in which non-responders from groups (2) and (4) (i.e., those receiving sham tDCS) receive a course of active tDCS using the same parameters and montage of phase I, that is, a direct current of 2 mA (current density = 0.13 mA/cm^2^) for 30 min/day for 24 days, in respective six brain regions.

Phase III is the longitudinal study of NeuroAD in which all active-tDCS responders—that is, responders from groups (1) and (3) from phase I and responders from phase II will be enrolled in a bi-monthly 1-year follow-up. Thus, two months after the last session, the participants will receive ten consecutive tDCS sessions (from Monday to Friday), which will be repeated every other month, until completing a one-year period (totaling 70 follow-up sessions). The tDCS parameters will be the same as those applied during the period between baseline and post-treatment, and the same cortical areas will be stimulated.

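### The primary ANOVA has a 12-month level by assigned tDCS, but no 12-month assessment of sham-only patients is described, so that contrast is not a comparison with placebo

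*Protocol article*

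**What the plan says.** All references are to the protocol article.

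- **Proposed Analysis.** For the primary ADAS-Cog analysis: "The within-subject variable will include time (baseline, post-treatment and 12-month follow-up". On the grouping factor: "the effects of the treatment condition (active or placebo tDCS; active or placebo cognitive intervention) will be examined as a between-groups variable". The same strategy is applied to every secondary outcome. The analysis is intention-to-treat. For missing data, one of four methods is to be chosen: last observation carried forward, complete cases, likelihood-based methods or multiple imputation.
- **Abstract.** The study is said to allow the investigators to "assess, both in the short and long term, whether tDCS is more effective than the placebo".
- **Stepwise Procedures, Phase I.** On the randomised, blinded phase: "This stage includes two measurement time points: baseline (week 0) and post-treatment (week 8".
- **Stepwise Procedures, Phase II.** After week 8, "non-responders from groups (2) and (4) (i.e., those receiving sham tDCS) receive a course of active tDCS". The Overview words this as an offer: "those who did receive sham tDCS and did not respond will be offered 24 open-label daily sessions of tDCS".
- **Overview, sham responders.** "those who showed response with cognitive intervention (real or placebo) and sham tDCS will be referred to other neuropsychological centers".
- **Stepwise Procedures, Phase III.** Those followed for a year are "responders from groups (1) and (3) from phase I and responders from phase II will be enrolled in a bi-monthly 1-year follow-up". All of them receive repeated courses of active tDCS during that year.
- **Stepwise Procedures, response.** Clinical improvement is a pre-to-post ADAS-Cog difference of at least three points.

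**The concern.** The ANOVA treats 12 months as a third occasion on which the randomised groups, including placebo tDCS, can be compared. The phase descriptions give no such occasion. Randomised treatment ends at week 8. Entry to the follow-up year depends on the outcome itself, and everyone in that year is treated with active tDCS.

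The primary result is at stake. A group-by-time test with three time levels mixes a randomised contrast (baseline to week 8) with one formed by response and crossover (12 months). A reader of the Abstract would take the 12-month part as evidence on tDCS against placebo, which it would not be.

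**Working it through.** **Inputs.** 25 patients in each of four groups, so 50 assigned active tDCS and 50 assigned sham (Sample Size). Expected improvement 3.76 points, SD 1.32 (Sample Size). Response at 3 points or more (Stepwise Procedures). The plan gives no figure for how many patients will have 12-month data, so there is none to reproduce.

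**Step 1: follow each route after week 8.**

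- Active tDCS, responder: enters Phase III and receives further active tDCS.
- Active tDCS, non-responder: no later assessment described.
- Sham, responder: referred elsewhere, no later assessment described.
- Sham, non-responder who accepts crossover and then responds: enters Phase III and receives further active tDCS.
- Sham, non-responder who accepts crossover and does not respond: no later assessment described.
- Sham, non-responder who declines: no later assessment described.

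No route leads a sham-only patient to a described 12-month assessment. The count is 0 of 50 whatever the response rate. The sham label is not empty at 12 months, but everyone under it has had active tDCS.

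**Step 2: how many assigned to active tDCS are followed.** Under a normal model,

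P(change ≥ 3) = 1 − Φ((3 − 3.76)/1.32) = Φ(0.576) = 0.718.

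50 × 0.718 = 35.9, so about 36 are followed and about 14 are not. For assumed response rates of 30% to 90%, 50 × 0.30 = 15 to 50 × 0.90 = 45 are followed.

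**Step 3: how many sham patients cross over.** This needs a sham response rate, which the plan does not give. Assume that all accept, SD 1.32, and mean change 0 in group 4 (sham tDCS, placebo cognitive intervention). Group 4 non-responders are then 25 × Φ(3/1.32) = 25 × 0.988 = 24.7. Group 2 (sham tDCS, active cognitive intervention) is varied:

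- mean 0: 24.7, total about 49 of 50;
- mean 1.88: 25 × Φ(1.12/1.32) = 25 × 0.802 = 20.0, total about 45;
- mean 3.0: 25 × 0.5 = 12.5, total about 37;
- mean 3.76: 25 × (1 − 0.718) = 7.1, total about 32.

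The number crossing over is thus anywhere from about 32 to 49 under these assumptions, and lower if some decline. The sham-only count at 12 months stays at 0.

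**Step 4: effect on the ANOVA under each listed method.**

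- *Complete cases.* Only Phase III patients have all three time points. Those assigned active tDCS are kept because they improved by at least 3 points at week 8; those assigned sham are kept only if they did not. The two sets of week-8 changes cannot overlap, even if tDCS does nothing, so the week-8 comparison is distorted too.
- *Likelihood-based methods.* Every week-8 score is kept, but no on-placebo 12-month data inform the 12-month contrast.
- *Multiple imputation.* The observed 12-month scores under the sham label all come from patients who had active tDCS, so imputed values do not describe placebo.
- *Last observation carried forward.* Week-8 scores stand in for 12-month scores in a progressive disease.

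**Step 5: timing.** For crossed-over patients the follow-up year starts after a second treatment course, so 12 months is not the same time since randomisation in both assigned arms.

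**The case against.** Five points can be made for the plan.

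1. *Sham-only patients may still exist at 12 months.* This stands. A reader might infer that nobody remains on assigned sham, but the documents do not say so. Sham responders are referred elsewhere with no active tDCS described, and crossover is only offered. What is missing is a described assessment of these patients, not the patients.

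2. *The article is condensed and in places implies follow-up for everyone.* The Abstract mentions a 12-month follow-up without restriction, the attrition criteria refer to follow-up for participants in general, the analysis is intention-to-treat, assessments are repeated at every step, and the flowchart in Figure 2 is not available here. This stands in part: the finding is a conflict to reconcile, not proof that the data cannot exist. But patients outside a step are not covered by repeating assessments within it. Even if all 100 were measured, the contrast would largely be immediate against delayed tDCS, not tDCS against placebo.

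3. *The follow-up has its own analysis.* The Proposed Analysis section plans Kaplan-Meier and Cox analyses of relapse, with Phase I group and crossover among the variables. This shows that crossover was recognised. It does not repair the ANOVA; it makes the 12-month level unnecessary.

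4. *The week-8 comparison is sound.* This stands unless complete cases are used. A reader might infer that the selection always contaminates week 8, but that is one of four candidate methods, and likelihood-based methods keep every week-8 score.

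5. *The bias has no firm size.* This stands. It is tempting to say that nearly every sham patient crosses over, but that needs a sham mean of 0 in both sham groups, which gives active cognitive intervention no effect, and full acceptance. It is equally tempting to quote the week-8 gain among selected responders as the 12-month bias. That gain is within group and at the selecting assessment; regression to the mean would shrink it, and followed crossovers were also selected for response.

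**Conclusion.** The concern holds as a conflict within the protocol article. The analysis section and the Abstract promise a 12-month comparison with placebo tDCS, while the Overview and Stepwise Procedures describe none. The 12-month group contrast, and any group-by-time test that includes it, is selected on response and confounded by crossover in both the primary and the secondary analyses.

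The firm figure is 0 patients followed at 12 months on sham only, which needs no assumption beyond the routes as written. The split of about 36 followed and 14 not followed among the 50 assigned active tDCS rests on the plan's mean, SD and 3-point criterion and a normal model. The number of crossovers rests on assumptions outside the plan. No size in ADAS-Cog points is claimed for the 12-month bias.

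The randomised comparison from baseline to week 8 is valid by design, and remains so provided that complete-case deletion on the 12-month score is not used.

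**What to change.** - Define the primary and secondary randomised comparisons as baseline to week 8 in all 100 randomised patients, by assigned group.
- Remove the 12-month level from those split-plot ANOVAs.
- Keep the Phase III scores and the planned Kaplan-Meier and Cox relapse analysis, labelled as uncontrolled follow-up of responders to active tDCS, including those who crossed over.
- Limit the Abstract's statement on tDCS against placebo to the short term.

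If the full protocol does assess every randomised patient at 12 months, the article should say so and state that the contrast compares immediate with delayed or offered tDCS. That would still not be a long-term test against placebo.

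The cost is wording in the analysis section and the Abstract, with no change to any patient's treatment. The downside is giving up a long-term efficacy claim that the described design cannot support.

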Considering the different evaluations with the same cognitive tests throughout the clinical trial, the improvement in the performance of these tests may result from practice and not from the intervention applied (Chelune, 2010; Goldberg et al., 2015). A RCI will be used; it serves to assess whether the changes identified comparing pre- and post-intervention data can be attributed to the procedures used or are mere oscillations, artifacts, or measurement errors (Jacobson and Truax, 1991) resulting from repeated practice effects (Chelune et al., 1993). The RCI, correcting for practice effects and using the Iverson’s standard error of the difference will be calculated based on the Duff’s (2012) formulae.

The follow-up analysis will calculate the primary outcome (i.e., a decline in cognitive state). As proposed in Phase 1, the same cutoff will be used to classify clinical improvement (3.76 points in the mean, with an SD of 1.33 points in the ADAS-cog). The primary outcome measure will be calculated considering the differences between clinical improvement and clinical relapse (or censored if relapse did not occur). Kaplan-Meier survival analysis will be used to calculate this outcome. To investigate interactions of risk factors, the following variables will be observed: demographics characteristics (age, gender, level of education), clinical condition (duration of illness, comorbidities and neuropsychiatric states) and “methodological” variables (Phase 1 group and crossover). The hazard ratio will be estimated using the Cox proportional hazards (to each predictor variable or covariate)”

Regarding safety, adverse effects will be analyzed in terms of the ratio in each group and period (before and after treatment) and analyzed using Fisher’s exact test. Multivariate regression will be used to identify predictors of response. The outcome variables will be tDCS and cognitive intervention, and the predictors will be age, gender, comorbidities and use of medication.

The effectiveness of the blinding will be analyzed by using the chi-square test, comparing the ratio between errors and correct responses. Furthermore, these tests will be compared between patients with clinical response and those who failed to improve.

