The expected significant improvement is reaching 3.76 points in the mean ADAS-Cog, with a SD of 1.32 points, according to Rabey et al. (2013). Thus, we consider the difference of at least three points in the ADAS-Cog and in the pre- and post-treatment measures to be clinical improvement. All participants with clinical improvement will be considered as respondents.

In all steps, the primary and secondary outcomes assessments will be repeated. The pre-intervention measurement is planned to be performed in the week before the intervention starts and the post-intervention measurement is planned for the first week after the intervention.

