## Anticipated Results

Considering there is a serious lack of factorial designs for clinical trials in non-invasive cerebral stimulation for AD patients, we aim to ameliorate that situation by observing the effect size and clinical effectiveness of each procedure, not only comparing this intervention against a sham (which could prove the efficacy, but not the clinical effectiveness), but also against a cognitive intervention. Further, we hope to broaden the treatment scope, promoting improvement in cognitive and functional aspects by stimulating different cortical regions, in addition to memory. Therefore, our study may generate key results for clinical practice and patient management throughout the disease.

Then, to the best of our knowledge, our study may be the first to apply a factorial design in non-invasive cerebral stimulation for AD patients, and not only comparing this intervention against a sham (which could prove the efficacy, but not the clinical effectiveness), but also against a cognitive intervention. Next, this factorial design will be able to observe the effect size and clinical effectiveness of each procedure, and will also be able to elucidate whether it would actually be feasible to apply the therapies alone or in combination. Further, we hope to broaden the treatment scope, promoting improvement in cognitive and functional aspects by stimulating different cortical regions, in addition to memory. Therefore, our study may generate key results for clinical practice and patient management throughout the disease.

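### The plan names eta squared as the between-arm effect size and does not commit to a signed ADAS-Cog difference, with a confidence interval, for each treatment

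*Protocol article*

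**What the plan says.** Proposed Analysis sets out a split-plot ANOVA of the ADAS-Cog score with "one intra-group variable and one inter-group variable": time (baseline, post-treatment, 12 months) and treatment condition. Follow-up comparisons are covered by a general line: "comparisons using Bonferroni correction will be performed where appropriate".

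The section then fixes two effect measures. Between arms, "the effect sizes regarding inter-group comparisons will be calculated using the eta squared". Within arms, "effect sizes regarding intra-group comparisons will be calculated by means of Cohen’s d using Hedges’ correction". The secondary outcomes are to be handled in the same way.

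Elsewhere the protocol sets itself a question about size. Anticipated Results says that "this factorial design will be able to observe the effect size and clinical effectiveness of each procedure". Sample Size expects a mean improvement of 3.76 ADAS-Cog points with an SD of 1.32. Stepwise Procedures defines response in points: "we consider the difference of at least three points in the ADAS-Cog", before to after treatment. No section names a between-arm difference in ADAS-Cog points, or an interval for one, as a result to be reported.

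**The concern.** The two measures are attached to the wrong comparisons. The randomised comparison, which carries the evidence on efficacy, gets a share of variance with no sign and no unit. The uncontrolled comparison, change within one arm, gets the signed and readable measure. Change within an arm combines any treatment effect with placebo response, practice and the natural course of the disease.

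Treatment condition also enters as one between-groups variable. If it is coded as four arms, an overall eta squared need not separate the effect of tDCS from that of the cognitive intervention. That separation is the reason for a factorial design.

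At stake is whether the published result answers the protocol's own question. A clinician who asks how many points tDCS adds over sham, and how precisely that is known, would not find the answer in either named measure. Neither measure can be set beside the 3.76-point expectation.

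**Working it through.** The protocol gives no eta squared value to reproduce. The check asks what eta squared would show under the protocol's own planning figures.

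**Inputs**
- Difference: 3.76 points (Sample Size).
- SD: 1.32 points (Sample Size), taken here as the SD of change within an arm. SDs of 3 and 6 are assumptions, added to show the range.
- Four equal arms of 25 (Sample Size; 1:1:1:1 in Randomization and Blinding), so each factor compares 50 with 50.
- Higher ADAS-Cog scores are worse. A gain below means a larger fall in score.

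**Formula.** For arm means of the change score, population eta squared = V / (V + SD²), where V is the variance of the four arm means. With baseline and post-treatment only, this equals partial eta squared for the group-by-time term. With the third time point the value would differ, but it would still lack sign and unit.

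**Direction.** If tDCS gains 3.76 points and the cognitive intervention adds nothing, two arms lie 1.88 above the overall mean and two lie 1.88 below it. Then V = 1.88² = 3.534, SD² = 1.32² = 1.742, and eta squared = 3.534 / 5.277 = 0.67. If tDCS loses 3.76 points, V is the same and eta squared is again 0.67.

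**Which treatment.** If the cognitive intervention gains 3.76 points and tDCS nothing, V is still 3.534. If each treatment adds 3.76/√2 = 2.66 points, the arm means are 5.32, 2.66, 2.66 and 0, and V = 2.66²/2 = 3.53. Both give 0.67 for the four-arm term.

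**Points.** Hold the gain at 3.76 and vary the SD:

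| SD | V / (V + SD²) | Eta squared |
|---|---|---|
| 1.32 | 3.534 / 5.277 | 0.67 |
| 3 (assumed) | 3.534 / 12.534 | 0.28 |
| 6 (assumed) | 3.534 / 39.534 | 0.09 |

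One clinical effect thus gives very different values, and four different truths give the same value.

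**What the difference in points would show.** The 95% CI half-width is t × SD × √(2/n), with n per side and no dropout:

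| SD | Factor, 50 v 50 | Arm v arm, 25 v 25 |
|---|---|---|
| 1.32 | 0.52 | 0.75 |
| 3 (assumed) | 1.19 | 1.71 |
| 6 (assumed) | 2.38 | 3.41 |

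These widths are on the scale on which the protocol states its expectations.

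**The case against.** The strongest reply is that nothing is lost. The ANOVA is run on raw ADAS-Cog scores, and post hoc comparisons of arm means are signed differences in points. Eta squared is a usual companion to ANOVA. The article does not say that mean differences will be withheld, and tabulated contrasts with intervals are commonly left to an analysis plan that is not shown here.

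Much of this stands. A reader might infer that the trial cannot state points gained over placebo. The documents do not support that, because the estimate can be obtained from the planned model. Nor would an unnamed confidence interval be a finding by itself. What remains is that the article does not leave the effect measure open. It names one for each type of comparison, and the one it names for the randomised comparison does not serve its stated aim.

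Three further inferences should be resisted.
- That within-arm d is the only directional measure in the whole plan. For follow-up, "The hazard ratio will be estimated using the Cox proportional hazards", with Phase 1 group among the variables. That measure is directional, but it concerns relapse and not points.
- That efficacy will be judged by significance in an active arm and none in placebo. The protocol examines treatment condition between groups and nowhere adopts that rule. It also plans a practice-corrected Reliable Change Index. That addresses practice, though not placebo response.
- That chance values of eta squared give the size of this problem. With no effect and 100 patients, a one-way four-arm eta squared exceeds 0.06 in about 11% of trials. The planned model has three time points. Its partial eta squared for group-by-time (6 and 192 degrees of freedom, so Beta(3, 96)) exceeds 0.06 in about 6%. The first figure does not describe this analysis.

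**Conclusion.** The point holds as a stated, inferior choice of reported effect measure. For the randomised comparison the plan fixes a quantity that is 0.67 for a 3.76-point benefit and for a 3.76-point harm, and that falls to 0.28 or 0.09 for the same benefit at assumed SDs of 3 or 6. It does not commit to the signed difference for each treatment that its own aims require.

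The numbers rest on equal arms, a change-score calculation, no dropout, and the reading of 1.32 as the within-arm SD of change. The lack of sign and unit depends on none of these. Design, data, test and power are unaffected. The weakness lies in what will be reported, and it should be put right before results are seen.

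**What to change.** In Proposed Analysis, replace the sentence on effect sizes with a commitment to report, from the planned model, the between-arm difference in mean ADAS-Cog change at post-treatment, in points, with a 95% CI, for:
- active v sham tDCS (groups 1 and 3 v 2 and 4);
- active v placebo cognitive intervention (groups 1 and 2 v 3 and 4);
- the combined arm and each single-treatment arm v double placebo.

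Post-treatment is the natural time point because the open-label crossover phase starts after it. If treatment enters as one four-level variable, all of these are linear contrasts of the arm means.

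A between-arm Hedges g can be added if a standardised size is wanted. Eta squared can stay as a supplement. Within-arm d should be labelled descriptive and not evidence of efficacy. The same rule should apply to the secondary outcomes. When the difference is read against the 3-point figure, the text should note that this figure defines response in an individual patient and is not a between-arm margin.

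The cost is a few lines of text and slightly more reporting, with no new data or patients. The published effects may look smaller than within-arm changes would.

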### Sample Size

The sample size was estimated based on previous studies that used paired tDCS groups in treating AD (Ferrucci et al., 2008; Boggio et al., 2012). The power calculations determining the number of participants in each group were made in relation to the expected change in ADAS-Cog because this instrument is commonly used in studies involving cognitive evaluation in these patients (Vellas et al., 2007; Balietti et al., 2017; Xiao et al., 2017).

The expected significant improvement is reaching 3.76 points in the mean, with an standard deviation (SD) of 1.32 points, according to Rabey et al. (2013). Therefore, a calculation considering the level of *p* < 0.05 and 90% power as significant suggests that at least 10 patients would be necessary in each group to detect whether the difference found matches the effect of the active or simulated treatment. Considering the application of tDCS in multiple areas, stimulation time and the possibility of sample losses throughout the study (dropout, inability to continue treatment, death), 25 patients per group will be included, totaling 100 participants.

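### The follow-up relapse analysis prints the planning group mean (3.76, SD 1.33) as the Phase 1 improvement cut-off, but the Phase 1 responder rule is at least three points

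*Protocol article*

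**What the plan says.** Three places in the protocol article bear on this point.

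- **Sample Size** introduces the figure as a planning value taken from an earlier study: "The expected significant improvement is reaching 3.76 points in the mean, with an standard deviation (SD) of 1.32 points". It is a group mean used for the power calculation.
- **Stepwise Procedures** repeats the same mean and SD (3.76 and 1.32) and then sets a rule for the individual patient: "we consider the difference of at least three points in the ADAS-Cog and in the pre- and post-treatment measures to be clinical improvement". It adds: "All participants with clinical improvement will be considered as respondents". The same section uses that status to route patients. For Phase II, "non-responders from groups (2) and (4) (i.e., those receiving sham tDCS) receive a course of active tDCS". For Phase III, "responders from groups (1) and (3) from phase I and responders from phase II will be enrolled in a bi-monthly 1-year follow-up".
- **Proposed Analysis** describes the follow-up analysis, in which time from clinical improvement to relapse is analysed by Kaplan-Meier and Cox methods and is called the primary outcome of that analysis. It says that "the same cutoff will be used to classify clinical improvement (3.76 points in the mean, with an SD of 1.33 points in the ADAS-cog").

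**The concern.** The Proposed Analysis sentence claims to carry over the Phase 1 cut-off but prints a different number, and one of a different kind. The Phase 1 rule is a threshold of three points for one patient. The printed figure is an expected group mean with its SD, which is not a threshold for classifying a patient.

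The relapse analysis starts from clinical improvement, so it needs the definition of improvement that admitted the patient to follow-up. If 3.76 is applied as printed, patients who improve by 3.0 to under 3.76 points are enrolled in Phase III as responders, with up to 70 further tDCS sessions planned, yet have no qualifying improvement from which to count time to relapse. The analyst would then have to drop enrolled patients or disregard the printed cut-off. If that choice is left until data are in hand, it can be influenced by the results.

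The randomised Phase I comparison, the sample size and the blinding comparison by clinical response do not depend on the misprinted figure.

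**Working it through.** **Comparison of the text.** No formula in the article produces a cut-off, so there is no derived figure to reproduce. The check is where each number comes from.

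| Section | Figure | Role in the text |
|---|---|---|
| Sample Size | 3.76, SD 1.32 | expected mean improvement, for power |
| Stepwise Procedures | 3.76, SD 1.32 | same expected mean, repeated |
| Stepwise Procedures | at least 3 | individual clinical improvement; defines respondents |
| Proposed Analysis | 3.76, SD 1.33 | called the Phase 1 cut-off for clinical improvement |

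The only individual threshold set for Phase 1 is three points, so the last row does not match its own attribution. The SD differs from the other two places by 0.01. That is numerically trivial.

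**How many patients lie between the two cut-offs.** Let X be a patient's improvement, taken as normal with mean m and SD s. The article gives no distribution of individual change. The SDs of 4 to 6, the mean of 0 and the sham means below are therefore assumptions. Only 3.76 and 1.32 come from the article.

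- Band = P(X ≥ 3) − P(X ≥ 3.76)
- Share of responders in the band = band / P(X ≥ 3)

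| m | s | P(X ≥ 3) | P(X ≥ 3.76) | Band | Share of responders |
|---|---|---|---|---|---|
| 3.76 | 4 | 0.575 | 0.500 | 0.075 | 0.131 |
| 3.76 | 5 | 0.560 | 0.500 | 0.060 | 0.108 |
| 3.76 | 6 | 0.550 | 0.500 | 0.050 | 0.092 |
| 0 | 4 | 0.227 | 0.174 | 0.053 | 0.234 |
| 0 | 5 | 0.274 | 0.226 | 0.048 | 0.176 |
| 0 | 6 | 0.309 | 0.265 | 0.043 | 0.140 |
| 3.76 | 1.32 | 0.718 | 0.500 | 0.218 | 0.303 |
| 0 | 1.32 | 0.0115 | 0.0022 | 0.009 | not informative (almost no responders) |

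**Phase III entrants affected.** There are 2 × 25 = 50 active-tDCS and 50 sham-tDCS patients. Sham non-responders cross over in Phase II and are assumed then to follow the active distribution. Before dropout:

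Count = 50 × band + 50 × (1 − P_sham(X ≥ 3)) × band

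| Active mean | Sham mean | s | Phase I part | Phase II part | Total |
|---|---|---|---|---|---|
| 3.76 | 0 | 4 | 3.8 | 2.9 | 6.7 |
| 3.76 | 0 | 5 | 3.0 | 2.2 | 5.2 |
| 3.76 | 0 | 6 | 2.5 | 1.7 | 4.3 |
| 3.76 | 3.76 | 4 | 3.8 | 1.6 | 5.4 |
| 3.76 | 3.76 | 6 | 2.5 | 1.1 | 3.7 |
| 0 | 0 | 4 | 2.7 | 2.1 | 4.7 |
| 0 | 0 | 6 | 2.2 | 1.5 | 3.6 |
| 3.76 | 0 | 1.32 | 10.9 | 10.8 | 21.6 |
| 0 | 0 | 1.32 | 0.5 | 0.5 | 0.9 |

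Totals are computed before rounding, so the parts may differ from them in the last digit.

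**The case against.** The strongest reply is that the operative words already point to the right rule. The sentence begins "As proposed in Phase 1, the same cutoff will be used to classify clinical improvement", and the only Phase 1 rule for a patient is three points. Stepwise Procedures gives the mean and SD first and derives the three-point rule from them, so the parenthesis may simply recall the origin of the rule. A figure labelled as a mean with an SD is awkward to use as a patient threshold, which makes the harmful reading the less natural one. On this view no patient is reclassified, and the counts above, which rest on assumed distributions, do not arise.

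Part of this stands. The benign reading is possible, the counts apply only on the literal reading, and their full range is wide. The top of that range treats the planning mean and SD as the distribution of individual change. It is also fair to say that the analysis affected is the follow-up of responders, not the randomised comparison.

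It does not remove the point. The sentence says what will be used to classify improvement and gives 3.76; three appears nowhere in it. Someone programming the analysis from that section alone would apply 3.76. On the benign reading the section still prints a wrong value as its decision threshold. The conflict is between two stated values, so it is not a detail left to a fuller document.

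A further reply is that correcting the cut-off does not define relapse, for which the article gives no threshold. That may be settled in the full protocol. It is no reason to leave the starting condition misstated.

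**Conclusion.** The concern holds. The cut-off printed for the follow-up relapse analysis is the planning mean, and it disagrees with the three-point rule that decides who crosses over and who enters Phase III.

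If 3.76 is applied as printed, with normal individual change, an assumed SD of 4 to 6 and a mean change between 0 and 3.76, about 4% to 8% of patients fall between the two cut-offs. That is about 4 to 7 Phase III entrants before dropout, or 9% to 23% of entrants. Over all cases tried it is about 1% to 22% of patients and about 1 to 22 entrants. If the parenthesis is only a misplaced planning statistic, the number reclassified is zero and the error is one of wording. The textual mismatch is certain; its effect on patients depends on which reading is applied. It should be fixed because it sits in the definition behind the follow-up's named primary outcome.

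**What to change.** In Proposed Analysis, remove the mean and SD from the parenthesis and state the Stepwise Procedures rule in their place: clinical improvement is a difference of at least three points in the ADAS-Cog between the pre- and post-treatment measures. It would be tidier to call this a reduction, since higher ADAS-Cog scores mean more impairment. Make the change before results are seen.

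The cost is one line of text. The three-point entry rule stays as it is, so crossover, Phase III enrolment, visits and sample size do not change.
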